### Participants

Participants may enter the trial if all the following apply: (1) they provide written informed consent, (2) they are patients with a functioning kidney allograft, (3) it has been at least 12 months after kidney transplantation, (4) they have an eGFR <30 mL/min/1.73 m^2^ according to Chronic Kidney Disease Epidemiology Collaboration (CKD-EPI) 2021 formula, (5) they are aged at least 18 years, (6) they can communicate in German, and (7) they attend regular follow-ups at KTC. Participants may not enter the trial if any of the following apply: (1) they have undergone multi-organ transplantation, (2) it has been less than 12 months after kidney transplantation, (3) they have an eGFR >30 mL/min/1.73 m^2^ according to CKD-EPI 2021 formula, (4) they are aged less than 18 years, (5) they cannot communicate in German, (6) they do not attend regular follow-ups at KTC, and (7) they enrolled in another interventional study less than 1 month before participation in this study. Additionally, support persons will be eligible if they are nominated by the patient as someone helping them cope with the consequences of their kidney transplant through support, encouragement, and communication. Support persons will be aged 18 years or older, German-speaking, and able to provide informed consent. Treating physicians who work at the participating clinics and use the AI-based decision-support system (DSS) will be eligible to participate in the study. Clinic staff will record the age and gender of nonconsenters who provided permission, which allows for the examination of consent bias.

### Sample Size

The primary analysis will be performed based on the frequency of conversations about treatment options after graft loss as perceived by the patient, which is assessed in a questionnaire after the respective consultation. Based on the data from Bissonnette et al [10], we estimate that in the control group, 10%-15% of patients will have a conversation about therapy options at the end of graft function. Regarding the intervention studied herein, we estimate that this frequency can be increased to 40%-45%, which is half of the effect size achieved by Bissonnette et al [10]. Using a 2-sided *χ*^2^ test, an α error of .05, and a power of 80%, 25-49 patients per group are needed. Estimating a dropout rate of 10% per year, this increases to 31-61 patients per group. Therefore, 61 patients per group were regarded as sufficient. In order to identify 122 participating patients, local study personnel will have to screen approximately 150 potentially eligible kidney transplant recipients over a period of 6 months.

### Randomization

Randomization will be performed using a predefined variable block randomization scheme using a web-based randomization service [18]. After screening for eligibility and assignment of the individual patient identifier, each patient-support person dyad can only be assigned once to 1 of the treatment arms. The sites will record the time of randomization.

### Blinding

Blinding of participants and study staff is not possible given the nature of the intervention.

### Intervention

#### Control Group: Routine Care

Routine care will be scheduled according to the current standard of care [19], which depends on the time after transplantation, medical condition, and other individual factors. Standard immunosuppression will be applied according to the international recommendations [20]. The prophylaxis and treatment of infections will follow the current standard of care as outlined in recent guidelines [21-26], for example, *Pneumocystis jirovecii* pneumonia prophylaxis for 4 to 6 months, cytomegalovirus prophylaxis according to the guidelines, and regular posttransplant BK virus monitoring according to guidelines [19]. Screenings for the antibodies against human leukocyte antigen once within the first 3 months, after 1 year, and every year thereafter, as well as in case of suspected rejection [27]. The overall medical treatment of kidney transplant recipients will be performed according to the Kidney Disease Improving Global Outcomes guidelines [19] and in patients with suspected rejection, a kidney biopsy should be performed and classified according to the most recent Banff criteria [28]. An integral part of the current routine aftercare is regular visits to the home nephrologist and KTC, where data are captured in an electronic health record [17]. Table 1 highlights the proposed schedule for posttransplant aftercare. The proposed schedule is adapted to the individual patient’s needs.

**Table 1 table1:** Frequency of routine visits in the outpatient clinic of the kidney transplant center (KTC) depending on time after transplantation.

Time after transplantation	Frequency of routine visits
Month 1	Once per week after discharge at the KTC
Month 2	Once per week
Month 3	Once per 2 weeks
Months 4 to 6	Once per 3 weeks
Months 6 to 12	Once per month
After 12 months	Once every 3 months

#### Intervention Group: AI-Supported Care

The kidney transplant recipients, who are randomized to the interventional arm, will receive identical routine posttransplant care as patients in the control group (see Table 1). In addition, the physicians in the KTC will be provided an AI-based decision support system making predictions for the risk of graft loss based on the patient’s most recent clinical, laboratory, and histopathology data, beginning from the second visit. A previous version of the AI-based decision support system has been studied in silico and in a reader study [11]. The physicians are provided a recommendation on how to proceed in case of a high-risk score. Briefly, physicians are recommended to inform the patients about this risk and discuss the potential necessity of return to dialysis or retransplantation, as well as planning, which mode of renal replacement therapy is preferred by the patient (hemodialysis, peritoneal dialysis, or listing for retransplantation by living donation). Depending on the patient’s preference, preparation for a smooth transition to dialysis or retransplantation should be performed.

### Outcomes

#### Primary End Points

For the primary end point, the frequency of conversations about treatment options after graft loss as perceived by the patient will be compared between the 2 groups at 12 months after randomization.

#### Secondary End Points

As the main secondary end points, the 2 different assessment tools for SDM, the CollaboRATE mean score and the Control Preference Scale (CPS; adapted version as used in previous studies [29]), are compared between the 2 groups at 12 months after randomization. The CPS is widely used as a validated tool to assess involvement in SDM [29,30]. However, it has been suggested that CPS may be misleading in some contexts of medical decision-making since it does refer explicitly to a “decision,” whereas, CollaboRATE is a brief process-orientated measure that recognizes that study participants may not always realize that a decision has been made or have difficulties focusing on 1 decision in the context of a complex care experience [31,32]. CollaboRATE has shown discriminative validity and interrater reliability. To supplement the quantitative outcome measures, qualitative data collection in the form of interviews will be performed and analyzed. All questionnaires and interview guides will be developed with the help of a multidisciplinary research group and pilot tested with patients and support persons to optimize acceptability and feasibility. Other secondary end points are summarized in Textbox 1.

Secondary end points and time frame after which they are assessed
**End points**
CollaboRATE mean score of all study visits from study inclusion until month 12 (values 0-9, higher values indicating better outcome)CollaboRATE mean score of all study visits from study inclusion until month 24 (values 0-9, higher values indicating better outcome)Mean Control Preferences Scale of all study visits from study inclusion until month 12 (values 1-5, higher values indicating better outcome)Mean Control Preferences Scale of all study visits from study inclusion until month 24 (values 1-5, higher values indicating better outcome)Frequency of kidney replacement therapy after graft loss at 12 monthsFrequency of kidney replacement therapy after graft loss at 24 monthsFrequency of emergency dialysis after graft loss at 12 monthsFrequency of emergency dialysis after graft loss at 24 monthsFrequency of dialysis initiation via arteriovenous-shunt after graft loss at 12 monthsFrequency of dialysis initiation via arteriovenous-shunt after graft loss at 24 monthsFrequency of dialysis initiation via permanent catheter after graft loss at 12 monthsFrequency of dialysis initiation via permanent catheter after graft loss at 24 monthsFrequency of retransplantation after graft loss at 12 monthsFrequency of retransplantation after graft loss at 24 monthsQualitative analysis of semistructured interviews after at 24 monthsQualitative analysis of physician-patient conversations after at 24 monthsFrequency of conversations about treatment options after graft loss as perceived by the patient will be compared between the 2 groups at 24 months

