**Methods:**

This is a 2-year, prospective, randomized, 2-armed, parallel-group, single-center trial in a German kidney transplant center. All patients will receive the same routine post–kidney transplant care that usually includes follow-up visits every 3 months at the kidney transplant center. For patients in the intervention arm, physicians will be assisted by a validated and previously published AI-based risk prediction system that estimates the risk for graft loss in the next year, starting from 3 months after randomization until 24 months after randomization. The study population will consist of 122 kidney transplant recipients >12 months after transplantation, who are at least 18 years of age, are able to communicate in German, and have an estimated glomerular filtration rate <30 mL/min/1.73 m^2^. Patients with multi-organ transplantation, or who are not able to communicate in German, as well as underage patients, cannot participate. For the primary end point, the proportion of patients who have had a conversation about their treatment options after graft loss is compared at 12 months after randomization. Additionally, 2 different assessment tools for SDM, the CollaboRATE mean score and the Control Preference Scale, are compared between the 2 groups at 12 months and 24 months after randomization. Furthermore, recordings of patient-physician conversations, as well as semistructured interviews with patients, support persons, and physicians, are performed to support the quantitative results.

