## Methods

### Study Design and Setting

The Prospectively investigating the Impact of AI on Shared Decision-Making in Post-Kidney Transplant Care (PRIMA-AI) trial is a 2-year, prospective, randomized, 2-armed, parallel-group, single-center trial in a German kidney transplant center (KTC). Patients more than 12 months after kidney transplantation with eGFR <30 mL/min/1.73 m^2^ and support persons will be randomized to routine care or to AI-supported care in a 1:1 ratio. During the study, 5 study visits are planned at the KTC—at randomization, and 3, 6, 12, and 24 months after randomization (Figure 1). In both groups, routine care visits will be scheduled as needed, depending on the patient’s medical condition and time posttransplant, which is usually every 3 months.

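### The CollaboRATE and CPS endpoints average in the Day 0 visit, before any AI use, which shrinks the between-group difference to 75% (12 months) or 80% (24 months) of the post-AI difference

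*Protocol article*

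**What the plan says.** **Endpoint window.** Textbox 1 lists four endpoints for shared decision-making:
- "CollaboRATE mean score of all study visits from study inclusion until month 12 (values 0-9, higher values indicating better outcome"
- "CollaboRATE mean score of all study visits from study inclusion until month 24"
- "Mean Control Preferences Scale of all study visits from study inclusion until month 12"
- "Mean Control Preferences Scale of all study visits from study inclusion until month 24"

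**Visits.** Study Design and Setting states that "5 study visits are planned at the KTC—at randomization, and 3, 6, 12, and 24 months after randomization". Table 2 ticks CollaboRATE and the CPS at all five visits, including Day 0.

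**AI exposure.** The intervention section has the system available to physicians "beginning from the second visit". The abstract says "starting from 3 months after randomization until 24 months after randomization". The AI row of Table 2 is blank at Day 0 and first ticked at month 3.

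**Wording elsewhere.** Secondary End Points calls the two instruments the main secondary endpoints and says they "are compared between the 2 groups at 12 months after randomization". It does not say which visits enter the score.

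**The concern.** The window in Textbox 1 opens at inclusion, while exposure to the intervention starts three months later. The Day 0 score therefore counts as outcome although the AI system cannot have influenced it. The endpoint is then a weighted mixture of an AI-exposed part and a part with no AI effect, so any real effect looks smaller than it is.

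Shared decision-making is half of the stated objective, and these are its main quantitative measures. At stake is a small or null difference being reported as evidence that AI support leaves shared decision-making unchanged, when part of the shrinkage comes from the endpoint definition.

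**Working it through.** **The plan's own figure.** The article gives no SD, effect size or power for CollaboRATE or the CPS. Its only calculation concerns the primary endpoint. It reproduces with the uncorrected two-sided chi-square formula at alpha 0.05 and 80% power: 10% versus 45% gives 25 per group, and 15% versus 40% gives 49. Two years of 10% dropout leave 0.9 × 0.9 = 0.81, and 25/0.81 and 49/0.81 round up to 31 and 61. Nothing below changes that.

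**Step 1: dilution (from the documents).** Let K be the number of AI-exposed visits in the window: K = 3 to month 12 (months 3, 6, 12) and K = 4 to month 24. Let D be the between-group difference in the mean of those K visits. The expected AI effect at Day 0 is zero, so the difference in the endpoint as written is

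(0 + K × D)/(K + 1) = D × K/(K + 1).

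- 12 months: 3/4 = 0.75, a loss of 25%.
- 24 months: 4/5 = 0.80, a loss of 20%.

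This needs complete visits and equal weights. It needs no SD or correlation, and the effect need not be constant over visits, because D is itself the average over the exposed visits. If a patient's mean were taken over available visits only, missed later visits would give Day 0 more weight.

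**Step 2: does the extra visit pay for itself? (assumed correlation)** Assume equal variances and a common correlation r between visits (compound symmetry), with r from 0.2 to 0.8. In units of the single-visit variance:
- post-AI mean: V_post = (1 + (K − 1)r)/K
- mean as written: V_all = (1 + K r)/(K + 1)
- sample-size ratio: (V_all/V_post) / (K/(K + 1))²

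Scale the effect so that a comparison of post-AI means has 80% power, that is, a standardised difference of 1.960 + 0.842 = 2.802. Power as written is then about Φ(2.802/√ratio − 1.960).

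| Window | r | V_post | V_all | SD ratio | Sample-size ratio | Power as written |
|---|---|---|---|---|---|---|
| 12 months | 0.2 | 0.467 | 0.400 | 0.926 | 1.52 | 62% |
| 12 months | 0.5 | 0.667 | 0.625 | 0.968 | 1.67 | 58% |
| 12 months | 0.8 | 0.867 | 0.850 | 0.990 | 1.74 | 56% |
| 24 months | 0.2 | 0.400 | 0.360 | 0.949 | 1.41 | 66% |
| 24 months | 0.5 | 0.625 | 0.600 | 0.980 | 1.50 | 63% |
| 24 months | 0.8 | 0.850 | 0.840 | 0.994 | 1.54 | 62% |

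To break even, the SD would have to fall by 25% (12 months) or 20% (24 months). It falls by at most about 7% or 5%.

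**Step 3: Day 0 as covariate instead.** Under the same assumptions, adjusting the post-AI mean for Day 0 lowers its variance to V_post − r². At 12 months this is 0.467 − 0.040 = 0.427 for r = 0.2 and 0.667 − 0.250 = 0.417 for r = 0.5. The 80% rises to about 83% and 94%. This holds only if Day 0 is a true baseline (see the fix).

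**The case against.** **These are secondary endpoints and no false positive arises.** This stands. Under no effect the expected difference is zero with or without Day 0, so type I error is not inflated. The mean over all visits is also estimated without bias for the endpoint as defined; the fault is that the endpoint is diluted. Each visit is scored separately, so no information is lost.

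**The power figures do not describe the planned analysis.** This also stands. Statistical Analysis names a chi-square test for secondary outcomes, whereas the table assumes a comparison of means with an assumed effect and correlation. A reader might infer that the trial has 56% to 62% power for CollaboRATE. The documents support no such statement; the figures only show the direction and rough size of the loss.

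**The endpoint is not defined in two contradictory ways.** A reader might infer a contradiction between Textbox 1 and the text saying that the scores "are compared between the 2 groups at 12 months after randomization". A cumulative mean up to month 12, compared at month 12, fits both. The text is looser, most of all for the CPS, which it does not call a mean. That is an ambiguity to tidy, not a proven conflict.

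**The analysis plan may adjust for baseline.** It may, and silence on covariates in a journal article is no fault. But adjustment alone would not take Day 0 out of an outcome that Textbox 1 defines as including it.

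**Conclusion.** The point holds for the endpoint window. Following Textbox 1 literally, the group difference in CollaboRATE and the CPS is 75% of the post-AI difference at 12 months and 80% at 24 months. That follows from the article's own visit schedule, given complete visits and equal weights. Under the assumptions of the illustration, the definition as written needs 1.52 to 1.74 times as many patients at 12 months, and 1.41 to 1.54 times as many at 24 months, as the post-AI mean for the same power.

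It should be corrected because it weakens the main secondary comparison for no gain. It does not touch the primary endpoint, the sample size of 122 or the type I error, and a reader should not take it as a threat to the trial's validity.

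**What to change.** - Define the 12-month CollaboRATE and CPS endpoints as the mean of visits 2-4 (months 3, 6 and 12), and the 24-month endpoints as the mean of visits 2-5 (adding month 24).
- Use the Day 0 score as a baseline covariate, provided it is completed before allocation is disclosed. Recruitment Process places the first study visit after randomization, and Blinding states that the trial is open, so Day 0 is before AI use but not clearly before the patient knows the arm. Removing Day 0 from the outcome cures the dilution even where this condition cannot be met; only the gain from adjustment then falls away.
- Use the same definition in the abstract and in Secondary End Points, where the wording is looser.
- Date the change before any between-arm look, so that it cannot appear data-driven.

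The cost is the rewording of four endpoint definitions and a slightly earlier questionnaire at visit 1. No new data are needed, since Table 2 already schedules every score.

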### Statistical Analysis

Preliminary analysis will involve computing descriptive statistics for all quantitative variables. For continuous variables, means, SDs, and quartiles will be estimated, while categorical variables will be summarized with counts and percentages in each category. Summaries will be performed by group and by assessment, as well as for the entire study group. Primary data analysis of the primary end point will involve comparing the frequencies of conversations about treatment options after graft loss between both groups using a 2-sided *χ*^2^ test. Secondary data analysis will include a comparison in secondary outcomes between both groups using a *χ*^2^ test. In general, test results will be described as significant if their *P* values are less than .05 without adjustments for multiple inferences. Multiple imputations will be used to deal with missing data.

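### The Control Preferences Scale endpoint is a 1-5 visit average with higher fixed as better and no anchors given; if its midpoint is shared control, it can score less sharing as improvement

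*Protocol article*

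**What the plan says.** The section *Secondary End Points* puts the Control Preferences Scale (CPS) in the top rank of secondary outcomes: "As the main secondary end points, the 2 different assessment tools for SDM, the CollaboRATE mean score and the Control Preference Scale" are to be compared between the arms at month 12. The Abstract adds month 24. The section says that an adapted version is used, citing earlier studies, and gives its purpose: "The CPS is widely used as a validated tool to assess involvement in SDM". Its one reservation is that the tool refers to a decision, which patients may not notice was made. It says nothing about what a high or low value means.

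The end-point textbox that follows gives the scoring: "Mean Control Preferences Scale of all study visits from study inclusion until month 12 (values 1-5, higher values indicating better outcome"), and for the later time point "Mean Control Preferences Scale of all study visits from study inclusion until month 24 (values 1-5, higher values indicating better outcome"). CollaboRATE, on 0-9, carries the same statement of direction.

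Table 2 collects the CPS at day 0 and at months 3, 6, 12 and 24, and starts the AI system at month 3. *Statistical Analysis* says: "Secondary data analysis will include a comparison in secondary outcomes between both groups using a" χ² test. It names no other test for secondary outcomes.

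**The concern.** The name of the instrument suggests a scale of who controls a decision. On such a scale sharing lies between the two parties, so a score that only gets better as it rises has one party deciding alone at its top. Reversing the code (x becomes 6 − x) swaps the ends and leaves the midpoint at 3. The article gives no reason why a higher value should mean more sharing.

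The trial's aim, beyond the frequency of conversations, is the effect of the AI system on shared decision-making. If the assumption about the levels is right, a main secondary result could be reported in the wrong direction, or real differences in sharing could cancel out in the mean.

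Three further difficulties do not depend on the levels: the average includes a visit before the intervention, it does not match the comparison described in *Secondary End Points*, and it is not the kind of variable the named test handles.

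**Working it through.** **The plan's own figures.** No sample size or power is given for the CPS. The stated sample size concerns the primary endpoint and reproduces: the uncorrected two-proportion formula (two-sided α 0.05, power 80%) gives 25 per group for 10% vs 45% and 49 for 15% vs 40%. Dividing by 0.9² gives 30.9 and 60.5, so 31 and 61. Nothing below changes this.

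**Part 1: direction.** Assumption, not stated in the article: level 3 is shared control, and levels 1 and 5 are one party or the other deciding alone. The distributions are illustrations, not figures from the plan.

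- Shift of 20% of patients from 3 to 5: change in mean = 0.20 × (5 − 3) = +0.4, read as better. Change in proportion shared = −20 points.
- Everyone at 3 (100% shared): mean 3.0. Half at 1 and half at 5 (0% shared): 0.5 × 1 + 0.5 × 5 = 3.0. The difference is 0.
- Everyone at 5 (0% shared): mean 5.0, the best possible score.
- Arm A, with 20%, 60% and 20% at levels 2, 3 and 4: mean = 0.4 + 1.8 + 0.8 = 3.0, with 60% shared. Arm B, with 10%, 30%, 40% and 20% at levels 2, 3, 4 and 5: mean = 0.2 + 0.9 + 1.6 + 1.0 = 3.7, with 30% shared. Arm B is read as better with half the sharing. Mean distance from 3 puts them in the opposite order: 0.4 for A and 0.9 for B, where lower is closer to shared.

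The same merging happens within a patient: a 1 at one visit and a 5 at the next average to 3.

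**Part 2: averaging over visits.** This needs no assumption about the levels.

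- Visits averaged to month 12: day 0 and months 3, 6 and 12, so four. Day 0 precedes the AI system. If the system shifts every later visit by a constant d, the expected difference in the average is (0 + d + d + d)/4 = 0.75d. To month 24 it is 4d/5 = 0.80d.
- *Secondary End Points* describes a comparison at month 12. The textbox describes an average from inclusion to month 12. As written, these are two different variables.

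**Part 3: the test.** With one whole-number score per visit, the sum of four visits runs from 4 to 20, so the average can take 17 values. A χ² test would have to treat these as unordered categories, with 122/17 ≈ 7 patients per value across both arms before dropout, or use a grouping the article does not state. A single-visit category or proportion does fit a χ² test.

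**Part 4: precision of a proportion.** Assume 50% vs 30% shared and 61 × 0.9 = 54.9, about 55 per arm, at month 12.

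- Standard error under no difference: √(2 × 0.4 × 0.6/55) = 0.0934.
- Standard error under the alternative: √((0.25 + 0.21)/55) = 0.0915.
- z = (0.20 − 1.96 × 0.0934)/0.0915 ≈ 0.18, so power is about 57%.

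**The case against.** The strongest reply is that the premise of Part 1 is not in the article. No section gives the response options or says what 1, 3 or 5 stands for. The version is adapted, its source is not shown, and the article describes the tool as measuring involvement. If the adapted version is coded so that values rise with involvement or sharing, the stated direction is coherent and Part 1 falls. Response options are also commonly left to the full protocol or the questionnaire, so their absence from a condensed article is no fault in itself.

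This stands, and it limits the point. A reader might infer that the scale certainly has sharing in the middle and that the direction is therefore an error. The article does not support that. It supports something narrower: range, direction and averaging are published as a fixed rule, that rule is right under one coding and wrong under another, and nothing in the text shows which applies.

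It is also fair to say that the 20% shift and the extreme arms are hypothetical, that nothing suggests patients often swing between 1 and 5, and that CollaboRATE, the recorded conversations and the interviews give other evidence on the same question. A comparison at month 12 could also be read as naming when the analysis is done rather than which visit it uses. None of this touches the day 0 visit or the mismatch with the χ² test.

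**Conclusion.** The concern holds conditionally. If level 3 of the adapted scale is shared control, the scoring rule is wrong for an endpoint on shared decision-making: it rates 0% sharing at level 5 above 100% sharing at level 3, counts a 20-point loss of sharing as a gain of 0.4, and cannot tell full sharing from an even split of the extremes. If values rise with sharing, the direction is sound.

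Under either coding, the visit average includes a measurement taken before the intervention (a constant effect is reduced to 75% at month 12 and 80% at month 24), differs as written from the comparison in *Secondary End Points*, and does not suit the only test named. These matter for one of two main secondary endpoints. They do not put the primary endpoint or the sample size in question.

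**What to change.** First state the levels and coding of the adapted version. Then:

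- **If the midpoint is shared control:** delete the statement that higher is better. Define the endpoint as the proportion of patients in the shared category at month 12, and again at month 24, compared by χ² test. Report the five-category distribution by arm.
- **If values rise with sharing:** say so and keep the direction. Leave the day 0 visit out of the mean, replace the χ² test with one suited to a score, such as a two-sample t test or a rank test, and align the wording of *Secondary End Points* with the textbox.

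Either way this is a change of wording, with the same questionnaire and visits and no new data. The first option has a price: a binary status at one visit is less precise than an average and sets aside the earlier visits, with about 57% power for the assumed 50% vs 30%. The result should therefore be reported with a confidence interval and read as supportive.
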